An unmet need for physicians is the availably of more objective tools for severity, frequency and context of BPSD, in order to apply non-pharmacological strategies (Loi and Lautenschlager, 2017). In Italy, 93% of physicians working in the field of dementia would be interested in a new tool to address BPSD, which reflects the unsatisfactory nature of current options (D'antonio et al., 2022).

Among BPSD, those belonging to the HIDA domain (hyperactivity, impulsivity, irritability, disinhibition, aggression, agitation) seem to be the most difficult to treat (Van der Linde et al., 2014; Keszycki et al., 2019). Person-centered strategies, including positive and significant social interactions, reminiscence therapy among others, seem to have a beneficial effect, albeit modest (Keszycki et al., 2019). A recent study evaluated caregiver burden and BPSD assessment with daily phone interviews over the course of eight days, showing that the quality of the relationship between caregivers and PwD attenuates caregivers stress related to BPSD (Chunga et al., 2021). Several instruments exist to evaluate caregiver burden, the most common being the Zarit Burden Interview (ZBI) (Melo et al., 2011; Liu et al., 2017; Griffiths et al., 2018; Evans et al., 2021; Jhang et al., 2021; Kanemoto et al., 2021), whose Italian version has been validated and is freely available (Chattat et al., 2011). The ZBI includes 22 questions, each scored with a 0–4 Likert scale, with a total score above 25 indicating a clinically significant burden. Generally speaking, the most burdensome BPSD include delusions, aggression, aberrant motor behavior, agitation and irritability, which substantially overlap with the HIDA domain (Fauth and Gibbons, 2014; Hiyoshi-Taniguchi et al., 2018).

A rather neglected field is satisfaction of caregivers for care provided by physicians to PwD. No instrument for healthcare satisfaction has been validated in caregivers of PwD, or in BPSD, and many instruments seem excessively long.^1^ On the other hand, there is a lack of instruments evaluating physicians satisfaction in treating PwD.

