**Figure 1 F1:**
[figure not shown]
Geographical distribution of involved centers. From North to South: Castellanza (west), Monza (east), Milan, Pavia, Padua (east), Florence, Chieti, Rome, Bari.

The dyads will be randomized in a 1:1 allocation ratio with a process of covariate adaptive randomization (Suresh, 2011), using caregiver age (cut-off 60 years old; this cut-off is chosen to ensure an equal representation of young/middle-age and elderly caregivers), patient comorbidity [Cumulative Illness Rating Scale (CIRS) – comorbidity index (Salvi et al., 2008) cut-off of 1], patient gender, patient functional independence [Activities of Daily Living (ADL) and Instrumental Activities of Daily Living (IADL) preserved vs. either of them not preserved] and baseline ZBI (cut-off of 31 points). Randomization will be performed through a dedicated software, as previously shown by other groups (O'Callaghan, 2014; Guillaumes and O'Callaghan, 2019).

At baseline, the following scales will be administered to the dyads: CIRS, ADL, IADL, NPI, ZBI, MMSE. These scales will be administered in a quiet environment, free of distractions. Data will also be gathered on age, gender, education of both caregivers and patients, and drugs used by the patients.

The caregivers randomized to the intervention arm will be instructed to use the BPSDiary to register specific behaviors of interest (the BPSDiary is available in the Supplementary material). These include insomnia, agitation/anxiety, aggression (either physical or verbal), purposeless motor behavior, delusions/hallucinations. The caregiver will have to mark any occurrence of these BPSD by indicating the time of onset, ticking the appropriate severity box (mild or severe) and writing down possible triggers. An introductory page explains the definitions of each term in plain language and provides examples. The data in the diary are then transposed on an interactive excel file (available at https://drive.google.com/file/d/1i3_NY7MRg9uoe2kD5njkUhax1zS9engp/view?usp=sharing) that allows the treating physician to analyze several aspects of the BPSD of the patient, such as their temporal pattern, severity, prevalence and triggers. The BPSDiary is only offered in a “paper and pencil” version, to avoid issues related with poor digital skills of elderly caregivers in Italy.

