Sample size has been computed with the software gpower (Erdfelder et al., 2009) considering a clinically significant difference of at least 6 points at the ZBI, corresponding to an effect size of 0.428 with a *t*-test. Considering α = 0.05 and β = 0.05, 238 would be required. We hypothesized a drop-out rate of 20%, based on clinical experience on similar studies; therefore, 300 dyads are required. The power graph is shown in Figure 2.

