**Figure 2 F2:**
[figure not shown]
Power graph for sample size calculation.

A *t*-test will be used to compare differences in ZBI variations (ZBI_followup_-ZBI_baseline_) between the two arms. A *t*-test will be also used to compare differences between the two arms in NPI, NPI-distress, olanzapine equivalents variations, as well as satisfaction questionnaires scores. Pre-specified analyses will include linear mixed effect models to compare ZBI trajectories, including arm, person's and caregiver's age, baseline MMSE, person's and caregiver's education, and olanzapine equivalents as possible predictors.

The registration data set is reported in Table 1. The CONSORT checklist (Schulz et al., 2010) for this RCT is available in the Supplementary material.

**Table 1 T1:** Registration data set.

**Data category**	**Information**
Primary registry and identifying number	ClinicalTrials.gov, NCT05977855
Date of registration	August 7^th^, 2023
Primary sponsor	University of Milano-Bicocca
Sources of monetary or material support	University of Milano-Bicocca
Contact for public or scientific queries	[name] [name] [[contact]], Fondazione IRCCS San Gerardo dei Tintori, Monza, Italy
Scientific title	Use of a diary to assess and manage Behavioral and Psychological Symptoms of Dementia [BPSDiary]
Countries of recruitment	Italy
Health condition or problem studied	Behavioral and psychological symptoms of dementia
Intervention	Diary to record five different BPSD vs. Standard of Care
Key inclusion and exclusion criteria	Inclusion criteria: - Neurodegenerative or vascular cognitive impairment (MCI or dementia) - Willingness of both caregiver and patient to take part in the study - Caregiver living with the patient, or able to cover the whole day - BPSD pertaining to the HIDA domain - Signed informed consent • Exclusion criteria: - Refusal to take part in the study
Study type	Interventional, non-pharmacological • Allocation: randomized • Masking: none • Primary purpose: treatment
Planned begin of enrollment	September 2023
Target sample size	300
Recruitment status	Recruiting
Primary outcome	ZBI variation at 3 months
Key secondary outcomes	- NPI variation - Olanzapine equivalents variation - Caregiver care-related satisfaction - NPI-distress variations^*^ - Caregiver and physician diary-related satisfaction

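### Baseline NPI is collected for every dyad but is not named as a covariate in the pre-specified ZBI mixed models, which forgoes a modest, nearly free gain in precision

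*Protocol article*

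**What the plan says.** All of this is in section 2 (Methods and analysis) of the protocol article, except the last item.

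- **Baseline data.** "At baseline, the following scales will be administered to the dyads: CIRS, ADL, IADL, NPI, ZBI, MMSE". The NPI is therefore available for every dyad before the intervention starts.
- **Allocation.** "The dyads will be randomized in a 1:1 allocation ratio with a process of covariate adaptive randomization". The factors are caregiver age (cut at 60), the CIRS comorbidity index (cut at 1), patient gender, preserved ADL and IADL versus not, and baseline ZBI (cut at 31).
- **Main comparison.** An unadjusted t-test on follow-up minus baseline ZBI.
- **Pre-specified mixed models of ZBI trajectories.** The possible predictors are listed as "including arm, person's and caregiver's age, baseline MMSE", the education of both members of the dyad, and olanzapine equivalents.
- **Rationale (section 1, Introduction).** "the most burdensome BPSD include delusions, aggression, aberrant motor behavior, agitation and irritability". The same section expects better assessment of these symptoms to lead in the end to lower burden.

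**The concern.** The eligibility rule asks for HIDA symptoms as judged by the physician. It sets no severity threshold and admits both MCI and dementia, so baseline symptom severity may vary widely. Severity is the collected covariate closest to the trial's own reasoning about burden. Yet it is balanced between arms by chance only and is not in the named model. The list contains antipsychotic exposure but not the symptoms that may prompt it.

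Two things are at stake in the adjusted ZBI analysis: residual variance that a measured covariate could remove, and the ability to answer a reader who sees the arms differ in baseline NPI. A covariate added after that difference has been seen would look data-driven.

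**Working it through.** **Inputs from the article (section 2, sample-size paragraph).** "considering a clinically significant difference of at least 6 points at the ZBI", "corresponding to an effect size of 0.428"; "Considering α = 0.05 and β = 0.05, 238 would be required"; 20% drop-out, 300 dyads, 1:1 allocation.

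**Derived.** Implied SD = 6 / 0.428 = 14.02 ZBI points. The article does not state this SD or say that it is the SD of change. Expected completers = 300 × 0.80 = 240, or 120 per arm.

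**Assumed.** r is the partial correlation of baseline NPI with 3-month ZBI. Given baseline ZBI, this equals the partial correlation with ZBI change. The article gives no value, so a range of 0.1 to 0.4 is shown.

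**1. The plan's own figure.** With d = 0.428, α = 0.05 and power 95%, the noncentral-t solution is 118.8, so 119 per arm and 238 in total. This matches, but only one-sided; two-sided needs 286. Two-sided power with 119 per arm is 90.8%. The sidedness is a separate matter and is noted only to fix the basis of the power figures below. Drop-out: 238 / 0.80 = 297.5, rounded up to 300.

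**2. Size of a chance imbalance.** The SD of the between-arm difference in a standardised covariate is √(2/n). With 119 per arm it is √(2/119) = 0.130 SD, so the 95% limit is 1.96 × 0.130 = 0.254 SD.

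**3. Effect on the ZBI difference.** Shift = r × 14.02 × imbalance. Unadjusted SE = 14.02 × 0.130 = 1.82 points; adjusted SE = 1.82 × √(1 − r²).

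**4. Gain in completers.** Gain = 240 / (1 − r²) − 240.

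| r | shift at typical (1 SD) imbalance | shift at 95% limit | adjusted SE | two-sided power, 119 per arm | extra completers |
|---|---|---|---|---|---|
| 0.1 | 0.18 | 0.36 | 1.81 | 91.1% | 240/0.99 − 240 = 2.4 |
| 0.2 | 0.36 | 0.71 | 1.78 | 91.9% | 240/0.96 − 240 = 10.0 |
| 0.3 | 0.55 | 1.07 | 1.73 | about 93% | 240/0.91 − 240 = 23.7 |
| 0.4 | 0.73 | 1.42 | 1.67 | 94.8% | 240/0.84 − 240 = 45.7 |

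Shifts and SEs are in ZBI points, against a target of 6. They use 14.02 as the SD before NPI is added. If baseline ZBI has already reduced that SD, the shifts and SEs shrink in proportion, while the completers column depends on r alone.

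**5. Validity of the unadjusted t-test.** In 40,000 simulated null trials of 119 per arm (simple 1:1 allocation, two-sided 5%), with NPI left out, type I error was 4.97% at r = 0, 4.95% at r = 0.3 and 4.97% at r = 0.5. The mean difference was about 0. Among the roughly 5% of trials whose NPI imbalance exceeded 0.25 SD, it was 9.0% at r = 0.3.

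**The case against.** A reader might infer that an imbalance in symptom severity passes straight into the primary ZBI result and biases it. The documents do not support that, for three reasons.

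- Randomisation leaves no bias on average, and chance imbalance is already in the t-test's standard error, as step 5 shows. The error rate rises only conditional on a large observed imbalance, which is uncommon.
- The predictor list belongs to the additional mixed models. Adding NPI there leaves the t-test as it is.
- The outcome is a change score and baseline ZBI is an allocation factor. Any association of NPI with the level of ZBI that is the same at both visits cancels in the change; only its association with later change remains.

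The premise also has limits. The Introduction ranks burdensome symptoms; it does not say that baseline NPI predicts change in burden. It cites a meta-analysis in which functional analysis improved burdensome symptoms without an effect on caregiver burden, and it criticises treating BPSD as one construct through broad tools such as the NPI. These are reasons to expect r at the low end, and to prefer a diary-domain score to the full total.

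Finally, the article lists possible predictors in condensed form, and a full analysis plan may add others. That stands: it cannot be said that NPI will never be adjusted for. What remains is narrower. The article chose to name its model's predictors, and the named set omits a relevant baseline measure that is already in hand.

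**Conclusion.** The point holds as a minor one about efficiency. Baseline NPI is measured on every dyad, is a plausible predictor of burden, and is absent from both the allocation factors and the named mixed-model predictors. The cost is a modest loss of precision, and of protection against an observed imbalance, in the adjusted ZBI analysis only.

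At r = 0.2 the SE would fall from 1.82 to 1.78 and two-sided power would rise from 90.8% to 91.9%. At r = 0.3 the figures are 1.73 and about 93%. At r = 0.1 the gain is negligible. Values at the lower end are more likely once baseline ZBI is accounted for. All of this rests on the assumed r and on an SD back-calculated from the stated effect size. The gain arises only if NPI enters so that it acts on the 3-month score.

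**What to change.** Before arm-coded data are seen, add continuous baseline NPI to the pre-specified ZBI model. The total over the diary domains is a natural choice, since the article already restricts NPI-distress to those domains. Either of two forms will do:

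- **In the trajectory model:** NPI plus an NPI-by-time term. A main effect alone shifts the ZBI level at both visits and does not adjust the change.
- **In a model of 3-month ZBI:** NPI as a covariate beside continuous baseline ZBI.

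Name the chosen form and NPI score in the analysis plan. The t-test on ZBI change can stay as written. The cost is one degree of freedom (3-month model) or two (trajectory model), a line of text, and no new data.

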## 3 Discussion

Several guidelines suggest the use of non-pharmacological interventions as a first line in the treatment of BPSD. However, the use of antipsychotics and other psychoactive medications is still common in Italy (Azermai et al., 2013), and this might be dependent on the fact that addressing triggers of disruptive behaviors is hard and heavily influenced by recall bias. Moreover, it seems that caregivers perceive systemic barriers in non-pharmacological interventions which are partially dependent on the inability of physicians to provide information, support, and coaching about such strategies (Kerns et al., 2018). On the contrary, caregivers might have the wrong idea that psychotropic medications are generally safe and effective, as they may not be aware of FDA black-box warnings on antipsychotics (Kerns et al., 2018). The use of the BPSDiary could theoretically allow for the identification of such triggers, which would help the clinician finding tailored non-pharmacological solutions for the management of BPSD. Moreover, it could allow caregivers to reflect on the mechanisms and causes of behaviors, which might give them a sense of empowerment.

A strength of our protocol is the representation of almost all Italian peninsula. Thanks to the variety of customs and societal characteristics in different Italian regions, the inclusion of centers representative of Northern, Central, and Southern Italy, as well as serving both Italian biggest cities (such as Rome and Milan) and smaller realities (such as Castellanza) will allow exploring the use of the diary in diverse settings, drawing considerations about its reception, adaptability, and implementation. This is important, as several disparities among Italian regions and contexts, such as living conditions, education, and social isolation, which are associated with varying levels of reported health (Franzini and Giannoni, 2010), may also influence the assessment and management of BPSD. Another strength is the large anticipated sample size, that will incidentally allow exploring secondary outcomes, as well as analyzing the effect of different variables such as specific dementia type to evaluate which kind of patient might benefit the most from the intervention.

We acknowledge that the inclusion of people with MCI might be controversial. On one hand, MCI people are usually not expected to be cared for by a caregiver, as their level of cognitive impairment should not significantly impact their daily activities by definition. On the other hand, we cannot exclude the fact that a caregiver might be indeed present for elderly people even when their cognitive impairment is still mild, especially when there are other comorbidities. Perhaps inherently to Italian society, it is still common to provide “care” for elderly relatives even when there is no loss of autonomy. Moreover, certain behavioral abnormalities might be indeed present in the early phases of certain neurodegenerative conditions such as DLB even in the “MCI” phase. For instance, the presence of hallucinations is a core feature of the 2020 McKeith's criteria of MCI-LB (McKeith et al., 2020). In other cases, MCI might be associated with a condition called mild behavioral impairment, which may increase the likelihood of progression of the cognitive impairment (Mallo et al., 2018; Ruthirakuhan et al., 2022).

A foreseeable limitation is the relatively short period of observation. However, this is comparable with the observation period used in other tools we used to evaluate concurrent validity, such as the NPI (Kaufer et al., 1998; Pozzi et al., 2023). Moreover, the inclusion criteria imply the presence of BPSD relative to the HIDA domain, which are associated with worse outcomes in PwD. Therefore, longer periods of observation could in theory increase the drop-out rate and therefore require an even larger sample size. A period of 3 months was judged to be a good compromise between all these considerations.

Another potential weakness is the decision to restrict BPSD assessment to only a certain subset of symptoms. Broad BPSD assessment tools that evaluate all possible disturbances already exist (Kales et al., 2017, 2018), but our intention was to target specifically those symptoms that greatly affect caregivers and result in worse outcomes for the PwD (Fauth and Gibbons, 2014; Hiyoshi-Taniguchi et al., 2018). On one hand, this will ensure that our tool is easy to use and understand, requiring caregivers to detect only the most striking behaviors, and also fast to complete, requiring only a minimum set of information to be provided. The decision to distinguish only two categories of severity (“mild” and “severe”) is in line with the perceived difficulty of caregiver to assign numbers to quantify behavior. As people of science, we tend to believe that numbers mean everything, but most of caregivers do not categorize their experiences mathematically, and forcing them to do so may result in some extent of arbitrariness that might jeopardize the assessment. We believe that our diary represents a good compromise between the two opposite tendencies of scientists and healthcare users, asking them to provide easy categories for analysis, but at the same time allowing them to reflect on and express freely their understanding of the triggers of BPSD of the PwD that they care for. While we did not conduct a proper feasibility study, during the preparation for the trial we proposed the instrument to 20 dyads at the Fondazione IRCCS San Gerardo and asked them about their opinions (qualitative data not shown). As expected, caregivers who were not cohabitating with patients reported greater difficulty in completing the diary, which led us to require cohabitation or ability to cover the whole day among inclusion criteria.

Finally, it could be argued that a “paper and pencil” diary could be somehow anachronistic in our hyper-digitalized society. However, our choice was mainly motivated by the fact that most of the caregiver that we expect to recruit will be quite old (i.e., spouses of enrolled PwD). While the creation of apps for senior citizens requires particular care regarding usability issues (Tajudeen et al., 2022), it is also possible that even a perfect app could fail in theory, due to specific country-related issues. Indeed, elderly Italian seem to have restricted digital skills compared to other countries (Caliandro et al., 2021; Melchior, 2023; Vainieri et al., 2023; Valokivi et al., 2023), which could represent a foreseeable barrier for the implementation of a study with an app. Therefore, we expect the paper version of the diary to be more acceptable by the majority of enrolled caregivers. Nevertheless, if the study will show promising results, it is our intention to try and develop an app version, possibly targeting younger caregivers.

## Ethics statement

The study was approved by the Ethical Committee “Comitato Etico Brianza,” with approval number 4251, on May 15^th^, 2023. Recruitment strategies will use different channels. First, the study will be proposed to PwD and caregiver meeting inclusion criteria and already attending the involved memory clinics. Secondly, the study will be advertised on the websites of the involved centers. Lastly, depending on local availability, the study could be advertised to a broader audience through coverage by local media (e.g., newspaper articles).
